### Target Volume definition

The treatment volumes are defined on the planning CT including the following volumes:*primary tumor (PT):* macroscopic tumor on contrast-enhanced MRI*gross tumor volume (GTV):* PT plus surrounding pseudo capsule, i.e. edema and edematous changes tissue including tumor cell contamination*clinical target volume (CTV):* GTV plus safety margins – 1 cm in lateral and ventro-dorsal direction, as well as 2.5 cm in proximal-distal direction. Natural borders are respected, i.e. skin or non-infiltrated bony structures as well as uninvolved compartments.*planning target volume (PTV):* CTV plus a circumferential safety margin of 0.5 cm.

Additionally, all relevant organs at risk (OAR) and normal tissue structures are contoured.

### Treatment technique and dose prescription

The treatment is performed with helical IMRT on the Tomotherapy HiArt System^©^ or with RapidArc^©^ IMRT as available. All treatments are performed with 6MV-photons and daily online CT-based IGRT.

A dose of 50 Gy in 2 Gy single fractions (5 fractions per week) is prescribed to the median in accordance with ICRU 83, with D_50%_ = 50.0 Gy. At least 95 % of the PTV must receive 95 % of the prescribed dose, i.e. D_95%_ > 47.5 Gy.

### Surgical treatment

Surgery is planned 5–6 weeks after completion of neoadjuvant RT. Re-staging including MRI as well as CT of the thorax is planned 4 weeks after RT. PET-examinations or any other imaging can be performed as required clinically.

If possible, the tumor will be resected surrounded by a layer of healthy tissue „en bloc“ in terms of an oncological radical resection ("wide/radical resection"). The resection entry channel from the diagnostic biopsy has to be included completely into the resection including the skin. An incomplete or reductive surgery is to be avoided. Reconstructive surgery for function preservation is anticipated. Curative approaches are the primary goal in situations when function and extremity preservation is not feasible.

The resection specimen must be clipped and marked so that correct anatomical reconstruction and correlation with imaging is possible. The surgeon will clip areas of potential incomplete resection on the resected tissue as well as in the tumor bed.

In cases of lymph node involvement on re-staging examinations in the area of the lymphatic spread of the tumor lymphadenectomy is performed. In cases of lung metastases after neoadjuvant RT or at the time of re-staging local control is still a priority, thus tumor resection is performed. Thereafter, any other measures necessary are taken, such as resection of lung lesions, chemotherapy, RT or other.

In cases of initial complete resection of the tumor direct closure of the wound is performed (Track A). If intraoperative rupture of the tumor occurs or if indication for hypobaric treatment or plastic surgery is present, vacuseal will be brought into the resection cavity and the wound is closed secondarily (Track B and C).

Within 5 days after tumor resection results of the pathological evaluation are available.

If the tumor is resected completely (R0), vacuseal is removed and the wound is closed (track B), if necessary with plastic surgery. If pathology reveals R1 status, secondary resection should be evaluated. If this is not possible with a function-preserving approach, local brachytherapy treatment in the resection cavity is performed. Thereafter, the wound is closed.

### Pathology assessment

For precise pathological evaluation precise orientation of the resected specimen is necessary, thus, it is recommended that a pathologist is present at the time of tumor resection. Classification of tumor resection margins is of high importance since the indication for local boost dose escalation is dependent on this result. Boost treatment should be performed on day 6–8 after resection. Pathological classification should therefore be performed within 5 days after surgery and resection margins (R0, R1, Rx) have to be communicated to the orthopaedic surgeon and the radiation oncologist.

Besides resection margins, tumor grading as well as further immunohistochemical stainings for exact pathological diagnosis will be performed. The tumor will be measured in all dimensions (in cm). Response to RT according to the established pathological protocol for osteosarcomas according to Salzer-Kuntschik will be evaluated [60]. Vital tumor cells will be evaluated as established also for osteosarcomas [61].

### Local dose escalation

In cases of R1 resection brachytherapy is anticipated in the 2. postoperative week. Brachytherapy catheters are implanted into the tumor bed depending on the size and location of the lesion.

Treatment planning is based on 3D-CT imaging with 3 mm slice thickness as well as the most recent MRI available.

The CTV_BRT_ for the brachytherapy application includes the R1-area plus a 5 mm safety margin, or a boost the complete resection cavity plus 5 mm safety margin. No additional PTV_BRT_ is added since the catheters are implanted directly into the target area.

Brachytherapy is performed using Iridium-192 High-Dose Rate (HDR)-afterloading. A dose of 12–15 Gy with 3 Gy single doses and 2 fractions per day (≥6 h between fractions) with D_90%_ for the CTV/PTV_BRT_ is applied.

### Further evaluations

To characterize the effectivity of neoadjuvant IMRT/IGRT for extremity sarcomas, the following evaluations will be performed:comparison of “conventional safety margins” and reduced safety margins within the protocols on treatment planning comparisons and calculation of dose reduction to normal tissueevaluation of tumor response on MRT as well as statement on resectability of the operating orthopaedic surgeon prior to resection based on imaging onlyhistopathological characterization of the tumor and tumor response to treatmentcorrelation of tumor response with outcome and prognosis.

### Inclusion criteria:

histologically confirmed and imaging defined soft tissue sarcoma of the extremitiesAJCC-Stage II or III (without T1a-tumos, no N1)primary or recurrent tumorafter biopsy or previous R2 resectionbased on imaging, „primary resectability“ or potential resectability after neoadjuvant RT must be presentage ≥ 18 yearsECOG Performance Status 0–2informed consent

### Main exclusion criteria

extraskeletal tumors of the Ewing-/PNET-groupextraskeletal osteo- or chondrosarcomaaggressive fibromatosis (desmoid tumors)dermatofibrosarcoma protuberanspresence of lymph node metastases (N1) or distant metastases (M1)expected survival < 1 yearpregnancy, adequate contraception until 3 months after RTsevere comorbidities impairing study treatmentsevere wound infections or recurrent skin infectionsknown positive HIV-Statussurgery of the primary tumor or chemotherapy within the last two weeks prior to study treatmentpersistent toxicity of other tumor treatments in the treatment regionsimultaneous chemotherapy, targeted therapy or experimental tumor therapyprevious RT in the treatment regionmedication with steroids or immuno-suppressants

### Follow-up

All patients are seen for a first follow-up visit 2 weeks after wound healing is completed, thereafter every 3 months during the first 2 years. The endpoints of the study are evaluated in detail during the first (2 weeks) and second (3 months) follow-up.

Functional outcome and QOL are documented prior to treatment and at year 1 and 2.

Treatment response and efficacy will be scored according to the RECIST 1.1 criteria.

### Sample size calculation

A total patient number of 50 with an expected 20 % rate of wound complications was calculated for the study; the intent to treat (ITT) collective includes all patients included into the trial which signed informed consent and were allotted a patient study number. The per protocol collective (PP) includes only those patients, whose study treatment was applied completely without any severe protocol deviations.

Analysis for the primary and secondary endpoints are performed on the ITT collective, and re-evaluated in the PP group. The primary endpoint is the rate of wound complications 3 months after wound closure, including the 95 % confidence interval. The secondary endpoints are analyzed with an explorative approach. The rate of wound complications per treatment track is evaluated as means including the 95 % confidence interval. Survival rates are determined using the Kaplan-Meier Method.

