**Methods/ Design:**

The trial is designed as a prospective, monocentric clinical phase II trial. The treatment is performed with helical IMRT on the Tomotherapy HiArt System© or with RapidArc© IMRT as available. All treatments are performed with 6 MV photons and daily online CT-based IGRT.

A dose of 50 Gy in 2 Gy single fractions (5 fractions per week) is prescribed. Restaging including MRI of the primary tumor site as well as CT of the thorax/abdomen is planned 4 weeks after RT. PET-examinations or any other imaging can be performed as required clinically. In cases of R1 resection, brachytherapy is anticipated in the 2nd postoperative week. Brachytherapy catheters are implanted into the tumor bed depending on the size and location of the lesion. Surgery is planned 5–6 weeks after completion of neoadjuvant RT. All patients are seen for a first follow-up visit 2 weeks after wound healing is completed, thereafter every 3 months during the first 2 years. The endpoints of the study are evaluated in detail during the first (2 weeks) and second (3 months) follow-up. Functional outcome and QOL are documented prior to treatment and at year 1 and 2. Treatment response and efficacy will be scored according to the RECIST 1.1 criteria. A total patient number of 50 with an expected 20 % rate of wound complications were calculated for the study, which translates into a 95 % confidence interval of 10.0-33.7 % for wound complication rate in a binomial distribution.

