### Endpoints of the study

The primary endpoint is the hypothesis that with preoperative IMRT/IRGT using small safety margins in combination with local dose escalation with brachytherapy in the R1 situation a wound complication rate of 20 % can be achieved.

Thus, the rate of wound complications up to 90 days after surgery is scored. Wound complications are defined asany surgery for wound treatment requiring local or general anesthesia including debridement, operative drainage, secondary or repeated wound closure including rotational plastic, any free tissue transfer or skin transplantations exceeding the procedures included into the protocolinvasive procedures without anesthesia, e.g. 3 x aspiration of seromain-patient wound treatment e.g. intravenous antibiotics<90 days treatments with wound dressing materials

Secondary endpoints of the study are determination of R0-resections, local control, metastases-free survival, overall survival, as well as acute and late toxicities of RT. This includes rates of extremity preservation, function of the extremity as well as quality of life (QOL).

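### The primary wound-complication rate is placed on every consented, numbered patient, although only operated patients can have the event, so any unoperated patient left in the denominator lowers the rate

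*Protocol article*

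**What the plan says.** The Sample size calculation section of the protocol article defines two analysis sets. For the first, "the intent to treat (ITT) collective includes all patients included into the trial which signed informed consent and were allotted a patient study number". For the second, "The per protocol collective (PP) includes only those patients, whose study treatment was applied completely without any severe protocol deviations". It then assigns them: "Analysis for the primary and secondary endpoints are performed on the ITT collective, and re-evaluated in the PP group".

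The endpoint is tied to surgery wherever it is described. The Endpoints section scores wound complications up to 90 days after surgery, and the Sample size section gives the rate at 3 months after wound closure. The target in the Endpoints section is that "a wound complication rate of 20 % can be achieved".

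The planned size is given as "A total patient number of 50 with an expected 20 % rate of wound complications was calculated for the study", and the abstract translates this into a "95 % confidence interval of 10.0-33.7 % for wound complication rate in a binomial distribution".

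On the way to surgery, the inclusion criteria accept primary resectability, or else "potential resectability after neoadjuvant RT must be" present on imaging. Under Surgical treatment, restaging is planned 4 weeks after radiotherapy and the operation 5-6 weeks after it.

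**The concern.** The population named for the primary analysis does not match the population in which the endpoint can be observed. A patient who withdraws, dies, refuses surgery or remains unresectable has no surgical wound. If that patient stays in the denominator, the reported figure is the product of two quantities: the complication rate among operated patients and the proportion operated on.

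The direction matters. The stated aim is to show that wound complications can be reduced, and the background quotes 35% after preoperative radiotherapy. Every unoperated patient kept in the denominator moves the estimate towards that aim. The usual reasons for ITT do not apply here: a single-arm trial has no randomised comparison to protect, and for a harm rate the full set is not the conservative choice.

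**Working it through.** **Inputs.** N = 50 and an expected rate of 20%, hence 10 events (Sample size calculation). Stated interval 10.0-33.7% (abstract, Methods/Design). Comparison rate 35% after preoperative radiotherapy (Background). The number not operated on is not given anywhere; 1 to 10 of 50 (2-20%) is assumed as a range.

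**1. The plan's own figure.** The exact (Clopper-Pearson) two-sided 95% interval for x events in n patients has lower limit Beta(0.025; x, n-x+1) and upper limit Beta(0.975; x+1, n-x). For 10/50 this gives 10.03% to 33.72%, which matches the article. Wald (8.9-31.1%) and Wilson (11.2-33.0%) do not match. The stated precision therefore treats all 50 patients as evaluable.

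**2. Dilution of the point estimate.** If k of 50 patients are not operated on and remain in the denominator, expected reported rate = operated rate x (50 - k)/50.

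| Not operated (k) | True 20% appears as | True 35% appears as |
|---|---|---|
| 0 | 20.0% | 35.0% |
| 1 | 0.20 x 49/50 = 19.6% | 0.35 x 49/50 = 34.3% |
| 3 | 0.20 x 47/50 = 18.8% | 0.35 x 47/50 = 32.9% |
| 5 | 0.20 x 45/50 = 18.0% | 0.35 x 45/50 = 31.5% |
| 10 | 0.20 x 40/50 = 16.0% | 0.35 x 40/50 = 28.0% |

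For dilution alone to turn 35% into 20%, the unoperated share would have to be 1 - 0.20/0.35 = 43%.

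**3. The same 10 events on the two denominators.** On the ITT set the result is 10/50 = 20.0% (10.0-33.7%) whatever k is. On operated patients:

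| Operated | Rate | Exact 95% interval |
|---|---|---|
| 49 | 20.4% | 10.2-34.3% |
| 48 | 20.8% | 10.5-35.0% (upper limit 34.99%) |
| 47 | 21.3% | 10.7-35.7% |
| 45 | 22.2% | 11.2-37.1% |
| 40 | 25.0% | 12.7-41.2% |

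The upper limit on 50 patients lies 35.0 - 33.7 = 1.3 points below 35%. It passes 35% once three patients are not operated on.

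**4. Planning precision at 20% with fewer operated patients.** 9/45: 9.6-34.6%. 8/40: 9.1-35.6%. Against the stated interval, the upper limit moves by 0.9 and 1.9 points.

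**The case against.** **Scoring is not stated.** A reader might infer that the plan counts unoperated patients as free of complications. No sentence says so. They could also be treated as missing or listed as not evaluable, and timing the rate from wound closure makes the last reading plausible. Such a rule could stand in a full protocol or analysis plan that is not shown. This stands, and it makes the bias conditional. It does not remove the point, because the article itself fixes the set for the primary analysis: "Analysis for the primary and secondary endpoints are performed on the ITT collective".

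**Non-operation may be rare.** Some resectability is required at entry. Nodal or distant metastases, expected survival under one year and severe comorbidities are excluded, and resection goes ahead even if lung metastases appear at restaging. This also stands: the frequency is unknown and these rules tend to limit it. If everyone is operated on, the bias is zero.

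**The shift is small.** With 5 of 50 unoperated, the shifts are 2 points at 20% and 3.5 points at 35%, within an interval about 24 points wide. That is fair for the point estimate. The upper limit is more sensitive because it lies so close to 35%.

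**A false-success reading goes too far.** One might compute the chance of 10 or fewer events when the true rate is 35%: 1.6% with 50 operated, 4.7% with 45, 12.2% with 40. The documents do not support using these as error rates, because they state no cut-off or test. The rise also partly reflects the smaller number operated on. The chance of an observed rate of 20% or less among operated patients is 2.2% (9 or fewer of 45) and 3.0% (8 or fewer of 40).

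**The per-protocol analysis would show it.** It does in part: if surgery belongs to the study treatment, unoperated patients drop out of that set, and the rates per treatment track concern operated patients. But the per-protocol set is secondary and also removes operated patients with severe deviations, whose wounds are relevant. Neither defined set is all operated patients.

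**Conclusion.** The concern holds as a mismatch between the stated primary analysis set and a postoperative endpoint. Followed as written, and without an exclusion rule elsewhere, the plan biases the primary rate downward by the unoperated share, in the direction of the trial's aim. Under the assumed 2-20% unoperated, the bias is 0.4 to 4 percentage points at a true 20% and 0.7 to 7 points at a true 35%. Three unoperated patients would be enough for the interval around 10 events to include 35%. That affects how the result is read, not a formal decision, since none is planned.

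The size rests on an assumed non-operation rate and on unoperated patients staying in the denominator as non-events. This is a should-fix. It would be wrong to conclude that dilution alone could produce the hoped-for fall from 35% to 20%.

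**What to change.** - For the wound-complication rate, define the primary analysis set as all enrolled patients who undergo resection of the primary tumour, regardless of radiotherapy completeness or protocol deviations.
- Report the number of enrolled patients not operated on, with reasons, next to the rate.
- Keep the ITT set for survival and the other oncological endpoints. The per-protocol re-evaluation can remain as a secondary analysis.
- Beside the interval for 10/50, state the planning precision for fewer resected patients, for example 9/45 (9.6-34.6%) and 8/40 (9.1-35.6%).

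The cost is amendment wording and a slightly wider stated precision. If 50 resected patients are wanted, enrolment would have to be 50/0.90 = 56 at 10% loss or 50/0.80 = 63 at 20%; that is a separate choice which this fix does not require. The set should be fixed before the outcome data are analysed, so that the denominator is not chosen with the results in view.

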## Discussion

Neoadjuvant RT is an established treatment approach for extremity sarcomas, showing beneficial results compared to postoperative treatment. A major downside are increased rates of wound complications compared to postoperative RT. However, with modern RT approaches such as IMRT and IGRT, treatment precision is optimized with daily image guidance.

In the past, large safety margins were necessary to provide optimal oncological treatment, however, these safety margins most probably also contributed to the high rates of side effects since large amounts of normal tissue were exposed to RT.

The use of modern techniques enables the radiation oncologist to deliver precise RT doses, therefore margins around the tumor can be reduced which leads to sparing of normal tissue.

The present study protocol prospectively evaluates the use of IMRT/IGRT as neoadjuvant RT in patients with soft tissue sarcomas of the extremity with the primary endpoint wound complications, which is the major concern with this treatment sequence. Besides complications rates, local control rates and survival rates, as well as QOL and functional outcome as well as treatment response parameters (imaging and pathology) are part of the protocol. The data of the present PREMISS study will enhance the current literature and support the hypothesis that neoadjuvant RT with IMRT/IGRT offer an excellent risk-benefit ratio in this patient population.

## Abbreviations

BRT: Brachytherapy
CT: Computer Tomography
CTV: Clinical Target Volume
GTV: Gross Tumor Volume
IGRT: Image Guided Radiotherapy
IMRT: Intensity Modulated Radiotherapy
IORT: Intraoperative Radiotherapy
MRI: Magnetic Resonance Imaging
PTV: Planning Target Volume
